# A pragmatic controlled trial to improve the appropriate prescription of drugs in adult outpatients: design and rationale of the EDU.RE.DRUG study

**DOI:** 10.1017/S1463423620000249

**Published:** 2020-07-09

**Keywords:** appropriate prescription, educational intervention, pragmatic trial

## Abstract

**Introduction::**

Pharmacological intervention is an important component of patient care. However, drugs are often inappropriately used. It is necessary for countries to implement strategies to improve the rational use of drugs, including independent information for healthcare professionals and the public, which must be supported by well-trained staff. The primary objectives of the EDU.RE.DRUG (Effectiveness of informative and/or educational interventions aimed at improving the appropriate use of drugs designed for general practitioners and their patients) study are the retrospective evaluation of rates of appropriate prescribing indicators (APIs) and the assessment of the effectiveness of informative and/or educational interventions addressed to general practitioners (GPs) and their patients, aimed at improving prescribing quality and promoting proper drug use.

**Methods and analysis::**

This is a prospective, multicentre, open-label, parallel-arm, controlled, pragmatic trial directed to GPs and their patients in two Italian regions (Campania and Lombardy). The study data are retrieved from administrative databases (Demographic, Pharmacy-refill, and Hospitalization databases) containing healthcare information of all beneficiaries of the National Health Service in the Local Health Units (LHUs) involved. According to LHU, the GPs/patients will be assigned to one of the following four intervention arms: (1) intervention on GPs and patients; (2) intervention on GPs; (3) intervention on patients; and (4) no intervention (control). The intervention designed for GPs consists of reports regarding the status of their patients according to the APIs determined at baseline and in two on-line Continuous Medical Education (CME) courses. The intervention designed for patients consists in flyers and posters distributed in GPs ambulatories and community pharmacies, focusing on correct drug use.

A set of indicators (such as potential drug–drug interactions, unnecessary duplicate prescriptions, and inappropriate prescriptions in the elderly), adapted to the Italian setting, has been defined to determine inappropriate prescription at baseline and after the intervention phase. The primary outcome was a composite API.

**Ethics and dissemination::**

The study was approved by the Ethics Committee of the University of Milan on 7th June 2017 (code 15/17). The investigators will communicate trial results to stakeholders, collaborators, and participants via appropriate presentations and publications.

Registration details: NCT04030468. EudraCT number 2017-002622-21

## Strengths and limitations of this study

This trial addresses a problem of great epidemiological, clinical, and socio-economic impact: the inappropriate prescription of drugs to adult patients in the outpatient setting.The definition of prescribing inappropriateness indicators adapted to the Italian context provides a useful tool both for the physician in the daily prescription activity and for the Local Health Units for the activities of evaluation and monitoring of the prescriptive performance.The use of existing data for baseline and outcome evaluation is a powerful and relative low-cost research tool that can be easily implemented on a larger scale. Despite this potential of prescription database analysis, a real measure of the appropriateness of prescriptions should be patient-based and evaluated by specialized personnel taking into consideration the characteristics of the patient.Since prescribing is uniquely managed by the doctor and is based on his/her final judgement, any intervention cannot impose decisions but only educate the doctor and support his/her activity; as a consequence, the integration of improved decision-making processes into the daily prescribing practice requires multidimensional interventions maintained over time.

## Rationale

Medicines are meant to improve health of patients; they do have, however, the potential to harm human subjects. The process of drug prescribing is therefore a fundamental component of the care of patients (World Health Organization, 2002). Appropriateness of prescribing is a balance of pharmacological rationality, the need of individual patients and economic aspects. It occurs when patients receive medications appropriate to their clinical needs, in doses that meet their own individual requirement, for an adequate time period and at the lowest cost to them and their community (World Health Organization, 2002). It can be defined as ‘the outcome of the process of decision making that maximizes net individual health gains within the society’s available resources’ (Buetow *et al*., 1997).

Optimization of drug prescribing has become an important public health issue worldwide (Hogerzeil, 1995; Dean *et al*., 2002; 2005). That is because evidence indicates high prevalence of inappropriate prescribing of medicines, especially in elderly people, which are characterized by chronic conditions and multimorbidity, leading to an increased use of drugs (polypharmacy). Inappropriate prescribing occurs, for example, when the physician prescribes an incorrect dosage and/or duration of treatment, drugs with significant drug–drug and drug–disease interactions, or fails to prescribe beneficial drugs (Spinewine *et al*., 2007). Notably, correct prescribing does not guarantee that drugs are used properly. Non-compliance to doctors’ prescriptions is very common (Casula *et al*., 2012). Therefore, patient involvement in the decision process could promote a conscious attitude, in compliance with the instructions received.

Inappropriate prescribing is associated with increased morbidity and mortality, increased cost of treatment, and decreased quality of life (Harrison *et al*., 2018). World Health Organization data show that more than 50% of all drugs are inappropriately prescribed or dispensed, and 50% of patients use them improperly (World Health Organization, 2002). Nearly 8% of medical examinations of patients with more than 65 years lead to the prescription of a Potentially Inappropriate Medication (PIM) (Goulding, 2004). Another European survey (Fialova *et al*., 2005) showed that 20% of elderly patients used at least 1 inappropriate medication, with substantial differences between Eastern Europe (41% in the Czech Republic) and Western Europe (range from 6% in Denmark to 27% in Italy). Using different definitions in various settings, observational studies showed that 21%–40% of patients have received at least one inappropriate medication (Liu and Christensen, 2002). In two cohort studies in Italy, 18% of elderly outpatients had one or more PIM prescriptions (Maio *et al*., 2006), and a substantial proportion of subjects was exposed to prescriptions at risk of potential drug–drug interaction (pDDI) (Tragni *et al*., 2013).

To limit the consequences of prescription of PIMs, improving rational use of drugs is a major focus to enhance quality and safety of care. It is thus necessary to implement a series of strategies, including information for healthcare professionals and the public from independent sources, which must be supported by well-trained staff (Hogerzeil, 1995). Different strategies have been developed and validated in this context (World Health Organization, 2002). Of note, interventions that included in-depth and updated education on drug therapy to physicians led to significant improvements in their performance/behaviour. Training and feedback control of prescribing should be associated with availability of on-line references for immediate identification and verification of potential erroneous prescribing (Thomas *et al*., 2008; Ostini *et al*., 2009). More generally, a good drug literacy allows more realistic perceptions and expectations, a shared medical decision making, and a responsible behaviour in using drugs. This approach seems promising and can be achieved through targeted campaigns of public education.

In this context, to measure inappropriateness is necessary to quantify the problem at baseline, to identify areas of concern which might require further review or development, and evaluate the effect of interventions (Donabedian, 1966). Moreover, the measure of inappropriateness in prescribing practice allows the physician to have a measure of his/her own performance, representing a point of comparison with colleagues within the same geographical area (Lovaglio, 2012) and a guide to intervene on critical situations of individual patients, besides having a general potential to raise physicians’ awareness about the topic. Given that prescribing is a mix of evidence-base for intervention with the drug, diagnosis, clinical judgement, and a certain element of clinical intuition, identifying objective measures of inappropriateness is extremely challenging (O’Connor *et al*., 2012b). Though, it is not surprising that the proposed indicators are umpteen, with different characteristics and potentials depending on the object of the measure and the context of application, and need to be updated and contextualized. Among them, the explicit criteria (O’Connor *et al*., 2012b; Masnoon *et al*., 2018; Curtin *et al*., 2019) are clearly defined statements, which highlight PIMs in particular clinical circumstances. They are mainly based on trial evidence, expert opinion, and consensus techniques (O’Connor *et al*., 2012a). The development of a simple, inexpensive, and time-efficient set of indicators which can be used routinely to evaluate prescribing practice and to assess the effectiveness of optimization strategies is therefore warranted.

In this context, the EDU.RE.DRUG (*Effectiveness of informative and/or educational interventions aimed at improving the appropriate use of drugs designed for general practitioners and their patients*) study has been designed to deeply investigate the prescribing practice among general practitioners (GPs) and the correct use of drugs by patients in two Italian regions and to assess the effectiveness of informative and/or educational interventions addressed to GPs and their patients, to improve prescribing quality, and to promote proper drug use.

## Methods and analysis

### Study design

EDU.RE.DRUG is a prospective, pragmatic, multicentre, open-label, parallel-arm, and controlled trial, started in April 2017 (see summary of study characteristics in Table S1, Supplementary material).

### Study setting and population

The clinical setting of the study is the general practice. The study population is composed by all GPs and all their adult patients aged ≥40 years from selected Local Health Units (LHUs) of two Italian regions, Lombardy and Campania.

### Data source and collection

In Italy, National Health Service (NHS) provides universal coverage largely free of charge at the point of delivery. The regions are responsible for organizing and delivering healthcare through the LHUs. The study data are retrieved from administrative databases containing healthcare data of all beneficiaries of the NHS in the LHUs involved: in 2017, about 2,800,000 beneficiaries for the 4 LHUs in Lombardy (Bergamo, Lecco, Mantova, and Monza Brianza) and 3,300,000 beneficiaries for the 4 LHUs in Campania (Avellino, Caserta, Napoli 1 Centro, and Napoli 2 Nord) (ISTAT, 1999). These databases, set up and constantly updated by regional or local health authorities, are:Demographic Databases, containing data on residents who receive NHS assistance (birth date and sex), and on GPs (birth date, sex, and number of patients).Pharmacy-refill Databases, containing data on drug prescriptions reimbursable by the NHS, including prescription date, dispensation date, the Anatomical Therapeutic Chemical (ATC) classification, marketing authorization code, number of boxes, and cost for NHS.Hospitalization Databases, containing data on hospital discharge at public or private hospitals of the regions, including the admission date, the primary and secondary diagnoses, and the date of discharge.

Compliance with national and European laws on personal data is guaranteed by LHUs through the generation of unique anonymous codes for each patient and each prescriber, providing guarantees in respect of the privacy of every citizen.

Data used in this project cover a time period ranging between the years 2014–2017 (baseline) and 2018–2019 (follow-up).

### Definition of performance indicators

For the evaluation of prescribing practice, patients in polytherapy were defined as having 5–9 or ≥10 single drugs prescribed in 1-year period.

Moreover, researchers selected some of the most commonly used drug classes (ACE-inhibitors [C09AA], angiotensin receptor blockers [C09CA], anti-asthmatics [R03], antibiotics [J01], proton pump inhibitors [A02BC], selective serotonin reuptake inhibitors [N06AB], serotonin-norepinephrine reuptake inhibitor [N06AX], and statins [C10AA]) to be described as percentage of patients on each treatment and as amount of defined daily doses (DDD) prescribed per 1000 inhabitants/die.

### Definition of inappropriate prescribing indicators

The research team reviewed the scientific literature on the topic and identified a set of indicators that had to:–be explicit indicators that require each prescription to be compared with a set of pre-defined standards, within the context of the individual patient;–be applicable and valid regardless of the patient’s clinical characteristics;–include only drugs available on Italian market and reimbursed by Italian NHS (which are therefore traced into administrative databases).

Prescription of pDDIs has been defined based on *MediRisk software*, developed by Medilogy group, based on INXBASE by Medbase, a Finnish company formed by experts in pharmacotherapy, which produces medical decision support databases to safeguard effective and safe use of drugs. INXBASE is a drug–drug interaction database containing short and concise evidence-based information concerning consequences of and recommendations for more than 20,000 drug interactions (Inxbase; https://www.medbase.fi/en/professionals/inxbase/). Interactions are classified according to clinical significance (from minor ‘A’ to contraindicated ‘D’) and documentation level (from ‘evidence from in vitro studies’ ‘0’ to ‘evidence from randomised clinical trials, systematic reviews, or meta-analyses’ ‘4’). In this project, two drugs were considered potentially interacting if their coverage periods (calculated since dispensation date and based on DDDs) overlapped of at least 1 day. Only pDDIs with major ‘C’ clinical significance excluded those with level of documentation ‘0’, and contraindicated ‘D’ clinical significance was considered.

Therapeutic duplicates (TDs) have been defined as two or more prescribed drugs from the same chemical subgroup (same ATC code at the fourth level but different ATC code at the fifth level) (Fulda *et al*., 2004) with at most 3 days between the two dispensation dates.

Only in the elderly population (aged ≥65 years), we defined the ERD-list (EDU.RE.DRUG list, Table S2 in Supplementary material) developed based on the updated Beers criteria (Radcliff *et al*., 2015), the STOPP&START criteria (O’ Mahony *et al*., 2018), and the EU-(7)-PIM list (Renom-Guiteras *et al*., 2015). The three lists were merged and adapted to Italian setting by selecting only drugs available on the Italian market and reimbursed by Italian NHS. Moreover, the selection was limited to drugs always to be avoided in elderly patients, excluding drugs that should be used with caution or avoided in certain patients with certain diseases or conditions, as these circumstances cannot be evaluated through administrative databases.

The appropriate prescribing indicators (APIs) in elderly comprised also high scores (≥3) of the Anticholinergic Cognitive Burden (ACB) scale (Boustani *et al*., 2008) and of the Sedative Load (SL) score (Linjakumpu *et al*., 2003) from the published lists, again selecting only drugs available on the Italian market and reimbursed by Italian NHS.

### Definition of appropriate use indicator

For each medication, adherence rate will be assessed for the following chronic therapies [ATC]:antidiabetics [A10B]anti-hypertensive drugs [C02, C03, C07, C08, C09]lipid-lowering drugs [C10A]anti-osteoporosis drug [M05BA, M05B].

Adherence will be measured through the proportion of days covered (PDC) calculation (Pednekar *et al*., 2019). PDC is defined as the number of days covered by medication divided by the total number of days in follow-up. For each prescription, the coverage will be calculated as total amount of drug divided by the specific DDD. PDC ranges from 0 to 1, with 1 corresponding to 100% medication adherence.

### Study intervention

The GPs and their patients have been assigned to one of the following arms (Figure 1):A: intervention on GPs and patients (LHUs of Napoli 2 Nord and Lecco);B: intervention on GPs (LHUs of Napoli 1 Centro and Bergamo);C: intervention on patients (LHUs of Avellino and Mantova);D: control group (LHUs of Caserta and Monza Brianza).

**Figure 1. f1:**
[figure not shown]
Design of the study and description of the four study groups

The intervention addressing GPs consists in:feedback reports, describing inappropriate prescription status (prevalence of each pre-defined indicator of performance and of inappropriate prescribing, as listed above, evaluated in 2016) of their patients in comparison to median levels of each own LHU.two free on-line CME courses about rational prescribing and appropriateness measurement. The first course was focused on the presentation of the project and on general aspects concerning the inappropriate prescribing in general practice and the categories of the most vulnerable patients, such as the elderly or poly-treated patients, with the presentation of clinical cases of possible inappropriate prescriptions. The second course concerned the measurement of APIs, the guided reading of reports, and recommendations for prescribing to the complex patient and for medication review.

Notably, participation to CME courses was not mandatory, as well as both the courses and the reports received at baseline would not necessarily lead to changes in GPs’ prescriptive behaviour.

The intervention designed for patients consists in flyers and posters distributed in GPs’ ambulatories and community pharmacies, focusing on correct drug use (efficacy/safety, adherence to GP indications, and self-medication).

Time frame dedicated to the sending of feedback reports and to the delivery of educational material was January–March 2018.

### Study outcome

The study outcome was a composite outcome of API of ERD list, pDDIs, and TDs. The primary end point was therefore defined as the variation of the median prevalence of the composite API after the intervention in the groups with the intervention on GPs (A+B arms) compared to baseline. The prevalence will be calculated at GP’s individual level as the ratio between subjects with the composite API and total GP’s over-40-year subjects.

The secondary end points comprised the (1) variation of the median prevalence of each single API and performance indicator after the intervention, (2) evaluation of difference in efficacy among different types of intervention, (3) identification of predictors of poor prescription appropriateness, (4) health technology assessment (HTA) of intervention implemented, and (5) level of GP satisfaction assessed through an ad hoc web-based questionnaire.

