### Sample size and statistical analysis

The study design is a non-randomized, open-label, cluster intervention. All experimental units (GPs and/or patients) in each cluster receive the scheduled treatment. Assuming that at least 40% of resident in the involved LHUs of the two regions (1.1 million in Lombardy and 1.3 million in Campania) receive at least one prescription during 1-year period, considering a type I error of 5%, a power of 80% would allow to detect, at LHU level, a difference in the reduction of inappropriateness prevalence of at least 5% between intervention and control group.

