#### Interventions effectiveness (pre-post analysis)

The primary and secondary outcomes will be evaluated in a 6-month period before intervention (pre-intervention phase, October 2016–March 2017) and in a 6-month period after the intervention (post-intervention phase, October 2018–March 2019). Depending on LHU and on type of data, administrative data usually require 3–6 months to be processed and made available. The difference (Δ pre-post) in the outcomes will be estimated separately for each LHU. Appropriate contrasts to compare Δ in the different groups of intervention and the corresponding confidence intervals will be estimated. The standard error for each contrast will be assessed by an appropriate normality assumption or, if this assumption is not plausible, by other methods such as the nonparametric bootstrap.

Since the study is not randomized, to consider the potential confounding due to physicians’ and patient’s characteristics, two additional analyses will be made at physician and patient level. Firstly, the Δ of each physician will be evaluated. A linear mixed regression model will be applied including the Δ as response variable and physicians and the LHU characteristics as well as the type of intervention as covariates. To take into account that physicians are clustered within LHU, a random effect for LHU will be considered. A generalized linear mixed regression model considering post-intervention prevalence of composite API as response variable will be estimated. In this model, patient-, physician-, or LHU-level covariates will be included. Two random effects will be considered in the model: one for the physician and one for the LHU. To take into account the baseline probability of being inappropriately treated, we will include in the model the prevalence of composite API for the patient’s physician evaluated before the intervention.

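### The primary end point is an uncontrolled before-after change in arms A+B, while the sample size rests on a between-group difference and no between-group contrast is made primary

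*Protocol article*

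**What the plan says.** Four sections of the protocol article bear on this.

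- *Study outcome*: the primary end point is the change in the median GP-level prevalence of the composite indicator "in the groups with the intervention on GPs (A+B arms) compared to baseline". Comparing the types of intervention is listed separately, as secondary end point (2).
- *Sample size and statistical analysis*: 80% power at a 5% type I error is claimed for "a difference in the reduction of inappropriateness prevalence of at least 5% between intervention and control group".
- *Interventions effectiveness (pre-post analysis)*: the pre window is the "6-month period before intervention (pre-intervention phase, October 2016–March 2017"), the post window the "6-month period after the intervention (post-intervention phase, October 2018–March 2019"). The change Δ is estimated per LHU, and then "Appropriate contrasts to compare Δ in the different groups of intervention" are to be estimated with confidence intervals. None of these contrasts is named as the primary one.
- *Study intervention*: each of the four arms has two LHUs, one in each region. Arms A and B receive the GP intervention. Arm C receives patient material only. Only D is labelled control: "D: control group (LHUs of Caserta and Monza Brianza"). Reports and material were delivered in January–March 2018.

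**The concern.** A before-after change in treated LHUs mixes the intervention effect with everything else that changed between the two windows, such as new drugs, reimbursement rules, safety warnings and an ageing population. Delivery began in January 2018, so the nine months from April to December 2017 lie between the windows with nobody exposed. Change in those months still counts towards the primary end point.

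The bias can go either way. A general fall in inappropriate prescribing would look like a benefit, and a general rise would hide one. As the end point is worded, a positive primary result could be claimed even if the LHUs without the GP intervention improved just as much. The primary claim would also concern a different quantity from the one on which the trial was sized.

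**Working it through.** **Step 1: the quantities side by side.** Let Δ be the post-minus-pre change.

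- *Study outcome*: Δ(A+B).
- *Sample size*: Δ(intervention) minus Δ(control).
- *Interventions effectiveness*: Δ per LHU, then unspecified contrasts between groups.

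If a drift s is common to all LHUs and the intervention does nothing, the first quantity has expectation s. The second has expectation s − s = 0.

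**Step 2: the plan's own figures.** The patient counts reproduce: 0.40 × 2.8 million = 1.12 million and 0.40 × 3.3 million = 1.32 million, against the stated 1.1 and 1.3 million. The 80% power can be neither confirmed nor refuted, because the article gives no baseline prevalence, no SD of LHU changes and no intracluster correlation, and does not say whether 5% is absolute or relative. It is not a simple patient-level calculation. With 1.2 million patients per group, power is close to 100% at every assumed prevalence from 10% to 50%, for an absolute or a relative 5%.

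**Step 3: effect of a common drift on the A+B test.** From the article: four LHUs in A+B. Assumed: no intervention effect, the same drift s in every LHU, normally distributed LHU changes with standard deviation SD, and a two-sided 5% t test on the four changes (3 df, critical value 3.18). The noncentrality is s / (SD/√4) = 2s/SD.

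| SD (points) | drift s (points) | 2s/SD | declared an effect |
|---|---|---|---|
| 1 | 1 | 2 | 29% |
| 1 | 2 | 4 | 76% |
| 1 | 3 | 6 | 97% |
| 0.5 | 1 | 4 | 76% |
| 2.1 | 2 | 1.9 | 27% |
| 2.1 | 5 | 4.8 | 87% |

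Under the same assumptions the A+B versus C+D contrast rejects in 5% of trials whatever s is, because s cancels.

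**Step 4: the price of the controlled contrast.** With equal LHU weights the standard error rises from SD/√4 = 0.50 SD to SD × √(1/4 + 1/4) = 0.71 SD. The largest SD of LHU changes that still gives 80% power for 5 points (two-sided 5%) is:

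| LHUs compared | t test | normal approximation |
|---|---|---|
| 4 v 4 (A+B v C+D) | 2.1 | 2.5 |
| 4 v 2 (A+B v D) | 1.5 | 2.1 |
| 2 v 2 (one arm v D) | 0.9 | 1.8 |

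These are thresholds, not estimates. They do not include a region term, which would take one more degree of freedom (8 − 3 = 5 instead of 6 for 4 v 4).

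**The case against.** The strongest reply is that a controlled analysis is already planned. The pre-post section applies to primary and secondary outcomes alike, and its contrasts of Δ are not confined to the secondary ones. The sample-size section has the same between-group quantity in view. On this reading, *Study outcome* names only the variable and the other two sections supply the comparison. It follows that the trial does not lack a controlled analysis, and a reader who inferred that would be wrong. The reply does not settle which result is primary, since *Study outcome* names A+B against its own baseline and ranks the comparison of interventions as secondary.

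Three further inferences are tempting but not supported.

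- *A very small drift is almost certain to be declared significant.* Suppose one GP per 1,000–1,500 of the 6.1 million beneficiaries, half of them in A+B (about 3,050 to 2,033), and an SD of GP-level change of 4–6 points. The standard error is then 4/√3050 = 0.07 to 6/√2033 = 0.13, and a 0.5-point drift is significant with probability 0.96–1.00. That treats thousands of GPs as independent, whereas the plan estimates Δ per LHU and fits a random LHU effect. Tested on four LHU changes, the same drift gives about 0.29, 0.11 or 0.07 at assumed LHU SDs of 0.5, 1 or 2 points.
- *The median end point conflicts with models on the mean scale.* The model of each GP's Δ is an additional analysis for confounding. The main analysis allows a bootstrap, which is compatible with medians.
- *A+B versus C+D isolates the GP intervention.* With eight non-randomised LHUs it removes only trends common to all of them. It also averages over any interaction between the GP and patient interventions.

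**Conclusion.** The point stands and needs correcting. The article fixes an uncontrolled change as primary, sizes the trial on a controlled one, and leaves the planned contrasts unranked. The direction of the problem follows from the text alone: a common drift over 24 months enters the primary end point in full and cancels from a between-group contrast.

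The size does not follow from the text. The 29%, 76% and 97% rest on an assumed LHU SD of 1 point, drifts of 1, 2 and 3 points and a t test on four LHUs. With a larger SD the false-positive rate for a given drift is lower, though the drift still biases the estimate by its full amount.

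**What to change.** Make the primary end point the difference between A+B and C+D in pre-post change of GP-level composite prevalence. Specify:

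- equal weights for LHUs or arms, so that patient material is balanced (A and C have it, B and D do not); weighting by number of GPs would not guarantee this;
- region accounted for;
- standard errors that treat the LHU as the cluster.

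Keep A, B and C each against D, the only untreated arm, as secondary. Report the A+B change from baseline as descriptive only. Align *Study outcome*, *Sample size and statistical analysis* and *Interventions effectiveness*, and say in the sample-size section whether the control group means D or C+D.

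No new data are needed, because all eight LHUs are covered by the same kinds of administrative database. It is still more than a change of wording. The trial is registered, and the article appeared in July 2020, after the 2018–2019 follow-up period. The change, and its date relative to data access, must therefore be declared. The statistical cost is a wider interval, with 80% power for 5 points at 4 versus 4 LHUs only if the SD of LHU changes is at most about 2.1 points. LHU-specific trends should be stated as a remaining limitation.

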#### Analysis of indicators

The indicators of performance and of inappropriate prescribing will be determined at baseline and after the intervention, by measuring the explicit indicators defined above within each GP on 1-year base. The unit of analysis will be the patient or his/her prescriptions, depending on the indicator, and GP identified as the clustering factor within each indicator will be examined.

The performance indicators will be evaluated separately on the subpopulations of 40–64 years and ≥65 years. Polytherapy will be evaluated as the percentage of patients with 5–9 drugs or with ≥10 drugs on total GP’s subjects in each age class. Prescription of selected drug classes (as listed above) will be evaluated as percentage of patients on each treatment on total GP’s subjects in each age class and as amount of DDD prescribed per 1000 inhabitants/die in each age class.

Regarding APIs, pDDIs and TDs will be evaluated on subjects ≥40 years old, while drugs in EDR list, ACB scale, and the SL score will be evaluated on subjects ≥65 years old. For each API, the percentage of patients with at least one prescription meeting the API criteria on total GP’s subjects in the specific age class will be determined.

Adherence will be calculated by selecting all patients with a first prescription for the medication of interest within 1-year period. Patients will be required not to have prior prescription of that drug in the year before the index date (defined as the date of the first prescription fill in the period for the selected therapy), to select only incident users. Patients will also be required to have 1 year of enrolment after the index date to allow complete adherence evaluation at 1 year of follow-up.

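### The composite is a crude share of all over-40 subjects, yet its ERD-list part can occur only from age 65, so the uncontrolled A+B change also moves with any net shift in list age mix

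*Protocol article*

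**What the plan says.** Study outcome names the components: "The study outcome was a composite outcome of API of ERD list, pDDIs, and TDs". It sets the GP-level prevalence "as the ratio between subjects with the composite API and total" subjects over 40 on that GP's list. The primary end point is the change in the median of these prevalences "in the groups with the intervention on GPs (A+B arms) compared to baseline".

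The components do not share an age range. Definition of inappropriate prescribing indicators restricts the first: "Only in the elderly population (aged ≥65 years), we defined the ERD-list". Analysis of indicators repeats this for the analysis, "while drugs in EDR list, ACB scale, and the SL score will be evaluated on subjects ≥65 years old" (the list is misprinted there), whereas "pDDIs and TDs will be evaluated on subjects ≥40 years old". The same section gives each single indicator a denominator from its own age class, and for another family of measures it says "The performance indicators will be evaluated separately on the subpopulations of 40–64 years and ≥65 years". The composite receives neither treatment.

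Interventions effectiveness sets the windows: October 2016 to March 2017, and October 2018 to March 2019. It also plans contrasts of the change between intervention groups and two additional models. One is at physician level, with physician and LHU covariates. The other is at patient level, with patient, physician or LHU covariates.

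**The concern.** The definition of a case changes at the 65th birthday, but the denominator does not. People aged 40–64 count in the denominator and can be cases only through a pDDI or a TD. From 65 they can also be cases through the ERD list. A GP whose list grows older will show a higher composite on unchanged prescribing, and one whose list grows younger will show a lower one. Because the primary end point compares A+B only with its own past, no control group removes this movement. If lists age over the two years, a true improvement in prescribing would be understated.

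**Working it through.** **The plan's own figures.** The article reports no composite prevalence and no age distribution. Its only design figure is a detectable difference of 5% between intervention and control at LHU level, with 80% power. The population counts beside it check: 0.40 × 2.8 million = 1.12 million and 0.40 × 3.3 million = 1.32 million, against 1.1 and 1.3 million stated. The 5% itself cannot be rebuilt, because no baseline prevalence, intracluster correlation or variance of the LHU-level change is given. The present point does not depend on it.

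**Identity for one GP.** Let w be the share of over-40 subjects aged 65 and over, and let q65 and q40 be the composite prevalences in the two age classes.

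P = w·q65 + (1 − w)·q40

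With prescribing unchanged within each class, a net change Δw gives

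ΔP = Δw·(q65 − q40).

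Split q65 into a65 (at least one pDDI or TD) and e (qualifies through the ERD list only), and write a40 for q40. Then

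ΔP = Δw·e + Δw·(a65 − a40).

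The first term exists only because of the ERD age limit. The second is an ordinary age gradient in pDDIs and TDs, which would move any crude over-40 prevalence.

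**Size of the ERD term.** The Rationale cites 18% of elderly outpatients with a PIM in two Italian cohort studies, and 27% for Italy in a European survey. Used as stand-ins for ERD-list prevalence (an assumption), they are upper bounds for e, because ERD-list patients who also have a pDDI or TD are already cases.

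| Net rise in w (assumed) | e = 18% | e = 27% |
|---|---|---|
| 0.5 points | 0.09 | 0.135 |
| 1 point | 0.18 | 0.27 |
| 2 points | 0.36 | 0.54 |

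Entries are points of composite prevalence, e × Δw.

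**Both terms together.** With assumed q65/q40 of 30/10, 40/10 or 50/15%, the gap is 20, 30 or 35 points, so a 1-point rise in w moves the composite by 0.20 to 0.35 points. Not all of that is due to the ERD list.

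**From GP to median.** The identity is exact for each GP. The median across GPs moves by the same amount if all GPs share the same shift and prevalences; otherwise the figures indicate order of magnitude.

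**After the change proposed below.** With w held at its pre-window value, Δw = 0 and the between-class drift is zero by construction.

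**The case against.** Several stronger readings are tempting, and the article does not support them.

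- A reader might set this drift against the planned 5% and call it a large fraction of the target. That 5% is a difference between intervention and control, whereas the drift is a movement within one group. The ratio compares unlike quantities.
- A reader might infer that the between-group contrasts fail unless all eight LHUs age alike. They need only similar average ageing between arms. Ageing common to the arms cancels, and every arm holds one Campania and one Lombardy LHU.
- A reader might count each patient who turns 65 as an artefact. Others turn 40 and enter the denominator, and older patients die. Only the net change in the share matters.
- A reader might object that the 40–64 group dilutes the ERD effect. The study population starts at 40, two of the three components apply to all of it, and the undiluted ERD result is planned as a secondary end point on its own ≥65 denominator. A population-wide composite is a legitimate choice.
- A reader might see a contradiction with the age-split measures. There is none: pDDIs and TDs as single indicators are not split at 65 either.

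It can also be said that a condensed article leaves standardisation to the analysis plan, and that the patient-level model may adjust for age. The first does not fully answer the point, because the article itself fixes the primary prevalence as a crude ratio. The second concerns an additional analysis whose covariates are not named (age is named only for the determinants model), and it leaves the primary change as it is. The broader weakness, an uncontrolled before-after end point, is a separate matter; age drift is one small instance of it.

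**Conclusion.** The point holds as a small, correctable bias in a rule that the article states. A net change in the share of the list aged 65 and over moves the primary A+B change with prescribing unchanged, and no age standardisation is stated for that end point. The part due to the ERD age limit is at most about 0.18 to 0.27 points per 1-point net rise in the elderly share. Over 24 months on largely the same lists, the effect is probably tenths of a point or less. A rise masks a reduction; a fall would do the opposite.

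This rests on two assumptions: that the cited PIM prevalences are reasonable stand-ins for the ERD list, and that the net age shift is modest. The article gives no data on either. The direction and the mechanism follow from the definitions alone.

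**What to change.** For the primary Δ, compute each GP's composite in two strata, each on its own denominator: 40–64 years (pDDI or TD) and ≥65 years (ERD list, pDDI or TD). Combine them with fixed weights equal to the pre-intervention age shares, use those weights in both windows, and report both strata. Keep the crude over-40 prevalence as a supporting result.

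The cost is a little extra analysis on birth dates that the demographic databases already hold. Stratum values will be noisier for GPs with small lists. Two age bands also leave ageing within the ≥65 class uncorrected.
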